**Discussion:**

If effective at improving informed uptake of screening and reducing bias in participation, this invitation strategy could be adopted by local screening pilots or a national programme.

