### Setting and participants

Patients will be identified from primary care practices falling within three Clinical Commissioning Groups (CCGs): Islington, Camden, and City and Hackney. These sites were chosen because they have demographically diverse patient populations. All patients will be invited by their GP (by letter, including a clinic telephone helpline) to a pre-scheduled ‘lung health check’ appointment with two weeks’ notice. This will include an eligibility screen (i.e. smoking and medical history), spirometry test, CO reading, smoking cessation advice (for current smokers), and for those eligible, a LDCT scan. The appointments will be run by research nurses in outpatient clinics at a central London tertiary referral hospital and an inner London district general hospital (University College Hospital and the Homerton University Hospital). Informed consent will be taken by a research nurse at the beginning of each lung health check appointment who will explain that the purpose of the pilot is to measure uptake and will describe all other data being collected. Data on secondary outcomes will not be collected for patients who do not give consent.

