### Control invitation materials

Table 1 provides a detailed breakdown of the content, delivery and staging of information by invitation group. Invitations in both arms will be from the patient’s own GP. In the absence of ‘usual care’ invitation materials, control invitations will mimic so far as possible the best available materials and methods of established cancer screening programmes. These comprise the following:

**Table 1 Tab1:** Information content and delivery by stage and invitation group

	Delivery	Content	
	(mode, messenger, recipients, time)	Control arm	Intervention arm
Pre-invitation	Mailed 3–4 weeks prior to the appt From GP (signature and letterhead) All patients	Pre-invitation letter notifying the patient of the lung health check service Information booklet mimicking so far as possible ‘the facts’ booklets for cancer screening programmes	Identical pre-invitation letter to control Targeted information leaflet introducing the tests using a low burden approach including: - content designed to reduce fear, fatalism, stigma - explanation and diagram to show how early treatment can work - quotes from interview participants to address stigma and highlight benefit - emphasis on non-judgemental service
Invitation	Mailed 2–3 weeks prior to the appt From GP (signature and letterhead) All patients	Letter inviting patients for a lung health check including: - statement that smokers and ex-smokers are being invited - pre-scheduled appointment - contact details to cancel/rearrange/further information - information to help journey planning (map/address/stations/buses) Second copy of information booklet.	Control letter with one exception: - statement changed to say that people who have ever smoked are being invited (rather than smokers and ex-smokers specifically) Second copy of targeted information leaflet Brief essential information on the reverse side of the letter including details for requesting free copy of information booklet (phone or online)
Appointment	Run by Research Nurse All patients attending the appt	Information booklet (same as mailed previously). Nurse-led facilitation of informed decision-making	Identical to control

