### Intervention invitation approach: a targeted, stepped and low burden invitation strategy

The intervention group will receive the same stages of invitation materials as the control group. The two differences are: i) instead of the information booklet they will receive a targeted leaflet (see Additional file 1), and ii) the invitation and reminder letters will use indirect phrasing to say that smokers and ex-smokers are being invited. Together, these manipulations aim to deliver a targeted, stepped and low-burden approach to information provision prior to the appointment which, in principle, would be practically feasible to implement on a national scale. The group we are inviting will be far from homogeneous but as it is not feasible to ascertain each individual recipient’s characteristics prior to invitation, we are attempting to provide the best ‘one size fits all’ approach; inclusive enough to target a variety of different characteristics but also conservative, so as not to unnecessarily deter one group at the expense of another’s uptake. Materials have been tested during four patient and public engagement sessions to ensure acceptability and comprehensibility and reviewed by our multidisciplinary team (psychology, respiratory medicine, radiology, smoking cessation, and primary care) and community-academic partners from our qualitative phase of work informing the invitation design ([25]; full paper in prep).

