#### Secondary outcomes

To further explore interest and uptake of screening, willingness to be screened will be used as a proxy measure to gauge interest among those attending who are ineligible for a LDCT scan, and uptake of LDCT scans will be recorded among those eligible. Data on informed decision-making (i.e. objective and subjective knowledge, decisional conflict, decisional satisfaction) will also be collected at the appointment using a paper questionnaire. Items have been adapted from existing studies and measures, and low literacy scales have been chosen where available [44–46]. These measures will allow us to ensure the targeted invitation strategy does not compromise the ability of patients to make an informed decision about screening at their appointment. Scores on these measures will be compared by invitation group to ensure intervention participants achieve either similar or improved scores.

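### The informed-decision check compares only consenting attenders, a group the intervention is meant to change, so it needs covariate adjustment and a narrower conclusion

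*Protocol article*

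**What the plan says.** Secondary outcomes lists objective and subjective knowledge, decisional conflict and decisional satisfaction. These data "will also be collected at the appointment using a paper questionnaire". Their purpose is given as: "These measures will allow us to ensure the targeted invitation strategy does not compromise the ability of patients to make an informed decision". The sentence goes on to specify the decision about screening at the appointment, and the second of the secondary aims has the same target. Scores are to be compared by invitation group, and intervention patients are expected to do as well or better. Secondary analysis describes this as a check that the materials do no harm.

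The abstract's Discussion words the conclusion more broadly: "If effective at improving informed uptake of screening and reducing bias in participation", the strategy could be adopted by local pilots or a national programme.

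Three design features bear on the comparison:
- **Who is measured.** Setting and participants: "Data on secondary outcomes will not be collected for patients who do not give consent". Consent is taken at the visit, so only consenting attenders contribute.
- **What differs by arm.** Before the visit, intervention patients differ in that "instead of the information booklet they will receive a targeted leaflet", and in the phrasing of the letters.
- **What is the same.** At the appointment, Table 1 gives controls the information booklet and "Nurse-led facilitation of informed decision-making". The entry for the intervention arm is "Identical to control".

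**The concern.** The analysed group is formed after randomisation by attendance, which is the primary outcome. The intervention is designed to bring in people who would otherwise stay away. The section on the low burden of information anticipates low health literacy and numeracy in that target group. If the intervention works, its attenders will include more people likely to score lower, whatever the leaflet did to anyone's understanding. The check could then fail because recruitment succeeded. It could also pass for the wrong reason, for example if less-informed patients decline consent more often in one arm.

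Two further features limit what the scores can show. Both arms receive the same booklet and nurse support at the visit, which may dilute any difference caused by the mailed material. The decision to attend, which is what uptake means in the primary outcome, has no informedness measure. A statement that the check *ensures* no harm, or that uptake was informed, would claim more than the comparison supports.

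**Working it through.** **Inputs from Sample size:** 2000 patients, 1000 per arm; control attendance 35%; improvement 7%; two-sided 5% test; power 90%.

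**The plan's own figure.** For 35% v 42%, 1000 per arm, two-sided 5% and pooled variance, power is 89.6%, which agrees with the stated 90%. Read as a relative gain (35% v 37.45%), power would be 20.6%, so percentage points are meant. The primary sample size is not in question.

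**Who gives scores.**
- Control attenders: 1000 × 0.35 = 350. Intervention attenders: 1000 × 0.42 = 420.
- Total with full consent: 770 of 2000 = 38.5%. The other 61.5% of randomised patients give no score.
- Net extra attenders in the intervention arm: 420 − 350 = 70, and 70/420 = 16.7% of that arm's attenders.

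**Shift from selection alone.** Suppose the materials affect nobody's score, and the 70 extra attenders score *g* SD below the other 350 (assumption; also that nobody is deterred by the intervention). The intervention mean then moves by −*g* × 70/420:
- *g* = 0.2: −0.03 SD
- *g* = 0.5: −0.08 SD
- *g* = 0.8: −0.13 SD
- *g* = 1.0: −0.17 SD

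**Precision of the comparison.** The 95% half-width in SD units is 1.96 × √(1/n₁ + 1/n₂).
- Full consent, 350 v 420: 1.96 × 0.0724 = 0.14 SD.
- Consent 70% in both arms (assumption), 245 v 294: 0.17 SD.

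The shift is therefore small at the low end of the range and about as large as the half-width at the high end.

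**Would a composite over all randomised patients replace the check?** Suppose 70% of control attenders are adequately informed (assumption). Informed attendance is 350 × 0.70 / 1000 = 24.5%. With 420 intervention attenders the same 24.5% needs only 245/420 = 58.3% informed. A fall of 11.7 points among attenders would thus leave the composite unchanged, because the attendance gain offsets it.

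**The case against.** The strongest reply is that the protocol asks a narrower question. The aims and Secondary outcomes both refer to the decision at the appointment. The stepped strategy deliberately leaves complex information to the nurse. Only attenders face the screening decision, and the shared booklet and nurse support are part of the strategy under test. This stands. A reader might infer that the comparison cannot support any conclusion about informed decisions, but the documents do not bear that out: it is relevant to consenting attenders' decisions at the visit.

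A reader might also infer that the questionnaire follows the nurse discussion. Measuring decisional satisfaction hints at this, but the article says only that it is completed at the appointment. The selection problem is the same in either order.

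Informed uptake appears in one sentence of the abstract; the main Discussion speaks only of the strategy being shown effective, and the aims call this work exploratory. That also stands, so no formal adoption rule is at fault. The word *ensure* in Secondary outcomes remains too strong.

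The size of the shift is assumed, and for most of the range it lies inside the half-width. That is fair, but a bias does not average out as a sampling error does, and the protocol itself gives reason to expect its direction.

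The details of covariate models may sit in a full protocol or analysis plan that is not shown. Their absence is not the point. The article itself states the population, the comparison and the conclusion, and the conclusion is wider than the other two allow.

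**Conclusion.** The point holds in a limited form. The score comparison is restricted to consenting attenders, a group selected by the primary outcome, and so is not a protected randomised comparison. On the planned rates, and assuming that the 70 extra attenders score 0.2 to 1.0 SD lower, selection alone moves the intervention mean by −0.03 to −0.17 SD, against a 95% half-width of about 0.14 SD with full consent. The score gap, the absence of deterred patients and the consent rate are assumptions; the article gives no figure for any of them. Differential non-consent could act in either direction and is not quantified here.

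The comparison can inform a statement about decisions at the appointment among those who came and consented. It does not show that attendance itself was informed, and it cannot *ensure* absence of harm. The primary analysis and its sample size are unaffected.

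**What to change.** 1. **Adjust the comparison.** Adjust the between-arm score comparison for the variables that Demographics and smoking says are extracted for everyone invited: age, sex, ethnicity, IMD and smoking status. Add a sensitivity range for selection and non-consent, such as the range of *g* above with differing consent by arm.
2. **Narrow the wording.** Replace *ensure* and *informed uptake* with a conclusion limited to decisions about screening at the appointment among consenting attenders. State whether the questionnaire is completed before or after the nurse discussion.
3. **Keep any composite supplementary.** Informed attendance over all randomised patients may be reported as a description, with the knowledge cut-off set before unblinding. It should not replace the attender-only check, since a gain in attendance can mask lower informedness.

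The cost is a little more analysis and a narrower claim; no new data are needed. Adjustment removes only the selection explained by the recorded variables, so the sensitivity range is still needed.

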### Sample size

The target sample size is 2000 patients. This is based on an estimate that 35 % of patients in the control group will attend, similar to initial uptake of colorectal cancer screening (by FOBT) in London within the two most deprived IMD quintiles [47]. The aim is to achieve a 7 % improvement in uptake on the basis of similar previous research. Studies testing targeted ‘psycho-educational’ invitations have achieved a 5.9 % higher uptake of colorectal cancer screening (flexible sigmoidoscopy) in deprived areas [48] and an 11.8 % increase in FOBT participation [49]. Also, a 7 % increase would deliver clinically meaningful benefit if scaled to a national programme. With 2000 patients split equally into two groups, statistical power to carry out two-sided tests at the 5 % significance threshold is 90 %.

### Statistical analysis methods

#### Primary analysis

The researcher carrying out the analyses will be blinded to group allocation. Un-blinding will occur after the primary data analysis is complete and has been checked and verified by a second researcher. Chi square associations and multivariate logistic regression analyses will be carried out to compare uptake between the intervention and control groups. These analyses will take an intention-to-treat approach, including all patients identified and randomised. Due to the nature of this study, there should be no missing data for uptake.

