### Aims

The primary aim of this study is evaluate the impact of a targeted invitation strategy, compared with a control, on uptake of ‘lung health check’ appointments overall and in association with demographic and smoking characteristics.

The secondary aims of this study are to:compare the demographic and smoking-related characteristics of attenders versus non-attenders for each invitation group, and with the overall invited group,explore informed decision-making outcomes by invitation group to check that the information provided to each is equally effective in facilitating a patient’s ability to make an informed decision at the appointment,ascertain figures to help gauge uptake of a national screening programme and inform the feasibility of recruiting to a LDCT programme via primary care.

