#### Secondary analysis

Interaction terms will be used in regression models to investigate if there are differences in demographic and smoking-related predictors of uptake and if these are associated with invitation group. The demographic and smoking-related characteristics of attenders from each invitation group will also be compared with those of the overall invited group to further test for any biases in uptake and to elucidate figures which could be used to help gauge uptake by the high risk in the event of a national lung cancer screening programme.

Further analyses will be carried out to explore willingness to be screened, uptake of LDCT scans and informed decision-making outcomes (i.e. knowledge, decisional conflict, decisional satisfaction) by invitation group. This will function as a check that the intervention invitation materials do not adversely affect the patients’ ability to make an informed decision, given their low burden approach to information provision.

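### The un-blinding rule ends analyst masking at the verified primary uptake analysis, so masking is not secured for the interaction models that serve part of the primary aim or for the informed-decision check

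*Protocol article*

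**What the plan says.** All references are to the protocol article, the only document at hand.

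- **Masking (Primary analysis).** "The researcher carrying out the analyses will be blinded to group allocation". The next sentence gives the only release point: "Un-blinding will occur after the primary data analysis is complete and has been checked and verified by a second researcher".
- **Content of the primary analysis (same section).** "Chi square associations and multivariate logistic regression analyses will be carried out to compare uptake between the intervention and control groups". No interaction terms are mentioned.
- **Primary aim (Aims).** The effect of the targeted strategy "on uptake of ‘lung health check’ appointments overall and in association with demographic and smoking characteristics".
- **Interaction models (Secondary analysis).** "Interaction terms will be used in regression models to investigate if there are differences in demographic and smoking-related predictors of uptake", and whether these are associated with invitation group.
- **Other outcomes (Secondary analysis).** "Further analyses will be carried out to explore willingness to be screened, uptake of LDCT scans and informed decision-making outcomes". The section presents this as a check that the intervention materials do no harm to informed choice.
- **Expected direction (Secondary outcomes).** "Scores on these measures will be compared by invitation group to ensure intervention participants achieve either similar or improved scores".

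The Secondary analysis section says nothing about masking.

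**The concern.** Masking an analyst is most useful where the analyst has choices to make and the team has a result it hopes to see. Here the explicit protection is attached to a binary outcome, attendance, which nurses record before consent and for which no missing data are expected. The adjusted regression leaves some room for choice, and it is covered.

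Two later analyses leave more room:

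1. The interaction models need decisions on how to code age, ethnicity, deprivation and smoking.
2. The informed-decision comparison needs a view of what counts as similar scores, and the article states the result hoped for.

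These are not side issues. The abstract's discussion makes adoption depend on better informed uptake and on less biased participation. The first is judged from the decision-making scores. The second is judged from the interaction models and the comparisons of attenders with those invited. If the arms are known while these analyses are being settled, a favourable result is open to a suspicion of analyst bias that could have been avoided.

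**Working it through.** The point concerns the order of events, so the main check sets the sections side by side.

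| Analysis | Part of the primary aim? | Section | Masking stated? |
|---|---|---|---|
| Uptake by arm: chi-square, multivariate logistic regression | Yes (overall uptake) | Primary analysis | Yes, until complete and verified |
| Interactions of arm with demographic and smoking characteristics | Yes (second element of the aim) | Secondary analysis | No |
| Willingness, LDCT uptake | No | Secondary analysis | No |
| Knowledge, decisional conflict, decisional satisfaction | No, but the safeguard on the intervention | Secondary analysis | No |

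**Step 1.** The trigger is completion and verification of the primary data analysis.

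**Step 2.** As described, that analysis is the first row only.

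**Step 3.** The trigger can therefore be met while rows two to four are outstanding. Row two belongs to the primary aim.

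**Step 4.** Nothing in the article requires rows two to four to be finished first, and nothing forbids it. The strict conclusion is that masking is not secured for them.

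**Does moving the trigger change the design figures?** Inputs from Sample size: 35 % control uptake, a 7-point improvement (so 42 %), 1000 per arm, two-sided 5 %.

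- Mean proportion: (0.35 + 0.42)/2 = 0.385.
- Standard error under no difference: √(2 × 0.385 × 0.615/1000) = 0.02176.
- Standard error under the alternative: √((0.35 × 0.65 + 0.42 × 0.58)/1000) = 0.02171.
- Power: Φ((0.07 − 1.96 × 0.02176)/0.02171) = Φ(1.26) = 89.6 %.

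This agrees with the stated 90 %. None of these inputs depends on when the arms are revealed, so the change leaves them as they are.

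**How well would A/B coding hold?** After the primary analysis the analyst knows which coded arm had the higher uptake. If the true difference is the planned 7 points, it is 0.07/0.02171 = 3.2 standard errors, and the intervention arm would show the higher uptake with probability Φ(3.2), about 99.9 %. An analyst who guessed that the higher arm is the intervention would then almost always be right. If there is no true difference, the guess is right half the time. Coding therefore protects best when the effect is small or absent.

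**The case against.** **Lifting the mask after the primary analysis is not an error in itself.** This stands as a general statement. The rule deserves a change here because the article's own primary aim reaches past the primary analysis and because a safeguard on the intervention lies beyond the trigger.

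**The analyses may not be run unblinded.** A reader might infer that they will be. The article does not support this: the trigger sets an earliest point, the secondary analyses are undated, and the sentence that promises a masked analyst is not itself limited to the primary analysis. That sentence does, however, stand under the Primary analysis heading and is followed at once by the release rule. What survives is that masking is not secured.

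**The masked analysis is more than a simple test.** This is correct. It includes a multivariate regression, where covariate choice is one source of discretion, so it would be wrong to say that only a chi-square test is protected.

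**The mismatch is one of labels.** A reader might treat the interaction question as equal in weight to overall uptake. The article gives no such weighting: there is one primary outcome, and the sample size rests on the overall comparison. It is still named in the primary aim, and its analysis is headed secondary.

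**Pre-specification may already remove the discretion.** A full protocol, version 2.0, is cited but not shown, and an analysis plan may exist. If these fix codings and models, the gain from masking shrinks. The point therefore does not rest on missing detail; it rests on a rule that the article does state.

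**The analyst may have had no part in the materials.** A reader might infer that those who designed the leaflet will analyse it. The article does not say so, and it describes a second researcher and a steering group with independent members.

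**Masking may be guessed.** This stands, as the calculation above shows, and it limits the benefit.

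**Conclusion.** The point holds as a cheap improvement. The article states a rule that permits un-blinding before the interaction models and the informed-decision check are done. The first serves part of the primary aim; the second guards against harm from the intervention's low-burden information.

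No size can be put on the effect. A false-positive rate across several interaction tests would measure multiplicity, which masking does not cure, and would say nothing about the un-blinding rule. The exposure is limited to analyst choices: attendance is recorded by nurses, the questionnaires are completed at the appointment, and the overall comparison keeps its masking and its power of about 90 %.

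The conclusion assumes that the primary data analysis means what the Primary analysis section describes, and that no document not shown extends the masking. If one does, the article needs only to say so.

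**What to change.** Amend the un-blinding sentence so that the arms stay coded A and B until the interaction models and the analyses of LDCT uptake, willingness and informed decision-making are complete and have been verified by the second researcher, as already planned for the primary analysis. Compute differences in the decision-making scores as A minus B with two-sided intervals, and assign direction only at un-blinding.

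In the same edit, align the wording of the primary aim with the analysis headings, so that it is clear where the interaction question belongs.

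**Cost.** One sentence and a short delay before results can be read by arm. No new data or staff are needed, and sample size, alpha and power do not change. The remaining weakness, that a clear uptake difference may reveal the arms, should be acknowledged.

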### Randomisation and allocation procedure

The individual unit of randomisation will be the patient. A web-based randomisation programme has been constructed by an independent health research unit. This will randomise patients at a ratio of 1:1 using permuted blocks for each GP practice to ensure group allocation is evenly balanced by practice. Patient identifiable details will be concealed from the researcher carrying out the randomisation assignment using a pseudo-anonymised spreadsheet of eligible patient details exported securely to the researcher from the GP practice. Patients will be blind to their allocation and the research nature of the study, which would undermine the primary outcome.

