### Methods of data collection and outcome measures

#### Demographics and smoking

Data on age, sex, ethnicity, smoking status and postcode will be extracted from primary care records by practice administrators for all patients identified as eligible and invited. Postcodes will be converted to Index of Multiple Deprivation (IMD) scores and ranks on site by a researcher from a spreadsheet within which identifiable data fields have been hidden. A pseudo-anonymised spreadsheet containing all these data will then be compiled and exported to a researcher independent of the identification process for randomisation and entry into the study database. While developing this protocol, we surveyed members of the public and patients about accessing this data prior to consent and none interviewed had any objections.

At the appointment, these data will be verified by a nurse who will take informed consent for the collection of any further data post-attendance. Further data collection will include information on attendees’ highest level of education (as an additional measure of SES) and measures of smoking behaviour and history. These will include current smoking status (self-reported and CO verified), usual number of cigarettes smoked daily, age started smoking, pack-year history, use of other nicotine and tobacco products (pipes, cigars, electronic cigarettes, waterpipes, smokeless tobacco) nicotine dependence (two item Heaviness of Smoking Index) [43] and quit confidence within the next six months.

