#### Primary outcome

Uptake of the lung health check appointments will be recorded by the nurses running the lung health check appointments prior to consent. It will be measured by attendance because the outcome of interest is whether participants can be adequately engaged to consider lung cancer screening. The aim is to provide a realistic indication of uptake in a real-world clinical context. Recording attendance is already standard practice in a clinical context and knowing that participation is being recorded for research purposes would introduce observer bias and undermine the research question.

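### Randomisation is blocked by GP practice, but the primary analysis names an unstratified chi-square and a logistic regression without saying which decides or mentioning practice; the effect is small and the fix is free

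*Protocol article*

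**What the plan says.** Under Randomisation and allocation procedure, the protocol article states "The individual unit of randomisation will be the patient" and that the programme will "randomise patients at a ratio of 1:1 using permuted blocks for each GP practice". Practice is therefore a stratification factor and not a cluster.

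Under Primary outcome, uptake is binary: "It will be measured by attendance". Under Sample size, "The target sample size is 2000 patients", on the estimate that "35 % of patients in the control group will attend", with a hoped-for gain of 7%, two-sided 5% testing and 90% power.

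Under Primary analysis, one sentence covers the comparison: "Chi square associations and multivariate logistic regression analyses will be carried out to compare uptake between the intervention and control groups". It gives no order between the two methods, no covariate list and no reference to practice. Interaction models are placed separately, under Secondary analysis, so the article does distinguish tiers of analysis and puts both methods in the primary tier.

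Under Demographics and smoking, age, sex, ethnicity, smoking status and postcode (converted to a deprivation score) "will be extracted from primary care records by practice administrators for all patients identified as eligible and invited". These baseline variables are thus held whether or not the patient attends.

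**The concern.** There are two separate issues.

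**Practice.** Blocking was adopted "using permuted blocks for each GP practice to ensure group allocation is evenly balanced by practice". Once the arms are balanced within practices, differences in uptake between practices cannot contribute to the difference between arms. A crude chi-square still counts that variation in its standard error. The analysis then fails to claim precision that the design has secured. The article chose its three areas for their diverse populations, so variation in uptake between practices is plausible, although it is not quantified.

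**No decisive test.** The two methods can fall on opposite sides of 0.05, and the article does not say which would then carry the conclusion. They also estimate different things. The trial is sized on a difference in proportions, while the regression gives an odds ratio; for 35% v 42% this is (0.42/0.58)/(0.35/0.65) = 1.34.

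**Working it through.** **Inputs from the article:** 1000 patients per arm, control uptake 35%, gain 7 percentage points (42%), two-sided 5%, stated power 90%, individual randomisation blocked by practice, no missing outcome expected.

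**Assumed, because the article does not give them:** between-practice variation, number of practices, and strength of any covariate.

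**Step 1: the plan's own figure.** Pooled proportion 0.385.
- SE under the null = sqrt(0.385 × 0.615 × 2/1000) = 0.02176
- SE under the alternative = sqrt(0.35 × 0.65/1000 + 0.42 × 0.58/1000) = 0.02170
- Power = Φ[(0.07 − 1.96 × 0.02176)/0.02170] = Φ(1.26) = 89.6%

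The stated 90% is reproduced. A relative gain of 7% would give only about 21% power, so percentage points is the right reading. This is an unstratified two-proportion calculation.

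**Step 2: effect of ignoring practice in the chi-square.** Let ICC be the share of the outcome variance lying between practices. Blocking leaves only the within-practice share in the arm contrast, so the true SE is the crude SE × sqrt(1 − ICC).
- Crude SE / true SE = 1/sqrt(1 − ICC)
- Actual alpha of the crude test = 2[1 − Φ(1.96/sqrt(1 − ICC))]
- Crude power = Φ[(0.07 − 1.96 × 0.02176)/(0.02170 × sqrt(1 − ICC))]
- Stratified power: the same, with 0.02176 also multiplied by sqrt(1 − ICC)

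| Assumed ICC | SE too large by | Actual alpha, crude | Power, crude | Power, stratified |
|---|---|---|---|---|
| 0 | 0% | 0.050 | 89.6% | 89.6% |
| 0.01 | 0.5% | 0.049 | 89.7% | 89.9% |
| 0.02 | 1.0% | 0.048 | 89.9% | 90.2% |
| 0.05 | 2.6% | 0.044 | 90.2% | 91.1% |
| 0.10 | 5.4% | 0.039 | 90.8% | 92.4% |

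The loss is about 0.2 to 1.6 points of power for ICC 0.01 to 0.10. A logit-scale SD of 0.35 to 0.5 corresponds roughly to an ICC of 0.385 × 0.615 × SD², or 0.03 to 0.06. Simulation over that SD range, with overall uptake held at 35% v 42%, gave crude type I error of about 4.1 to 5.0% and about 0.6 to 1.0 points less power than a practice-stratified test, in line with the table.

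**Step 3: two unranked tests.** Null simulation with 20 practices of 100, blocks of 4 and 3000 runs per cell (Monte Carlo SE about 0.004). Success is counted if either the crude chi-square or a logistic regression with covariates but no practice term gives p < 0.05. Here the ICC is on the latent logit scale, and covariate strength is the log-odds per SD of the combined score.

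| Latent ICC | Strength 0.3 | Strength 0.6 | Strength 1.0 |
|---|---|---|---|
| 0 | 0.056 | 0.061 | 0.069 |
| 0.02 | 0.054 | 0.064 | 0.071 |
| 0.05 | 0.055 | 0.060 | 0.064 |
| 0.10 | 0.048 | 0.053 | 0.050 |

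The inflation comes from prognostic covariates. When the crude test was paired with a practice-stratified test and no covariate, the either-test rate was 0.050 to 0.051. With a moderate covariate (log-odds 0.5 per SD) and the SD range of Step 2, it was 5.3 to 6.2%.

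At latent ICC 0.10 the regression without practice rejected in 3.6 to 4.3% of null runs. A regression that omitted practice would therefore share the conservatism of the chi-square.

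**The case against.** The strongest reply is that an article may leave the covariate list to the full protocol or the analysis plan, and that practice may well be in the regression. This stands. A reader might infer that both primary analyses carry an inflated standard error, but the text supports that only for the chi-square, and only if uptake differs between practices.

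A second reply is that the article states no rule letting either test count, and that a crude comparison followed by an adjusted one is ordinary reporting. That is fair; the either-test figures show what the wording permits, not what is planned. The 9.75% that two independent tests would give does not apply, because the two tests use the same data and are highly correlated. Blinding the analyst to allocation does not settle the choice, since a two-sided p-value is the same whichever way the arms are labelled.

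A third reply is that the error is conservative and small. That also stands. A reader who simulates with 35% and 42% as rates conditional on practice (and on a covariate) will see crude power of about 83 to 88% and may infer that the trial is underpowered. In that set-up the overall difference is only 6.4 to 6.8 points, not the 7 on which the trial was sized.

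Nor does the article say that practice determines the hospital attended. It names three commissioning areas and two hospitals without mapping one to the other.

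What remains is that the article itself gives both methods primary status, ranks neither, and names an unstratified test after a stratified randomisation.

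**Conclusion.** The point holds in limited form and is minor. The crude chi-square is a valid but slightly wasteful test for this design: about 4 to 5% actual type I error and about 1 point of power lost at an assumed between-practice logit SD of 0.35 to 0.5. The planned power is essentially met either way. Leaving the decisive test open allows a type I error of about 5% without a strong covariate, 5.3 to 6.2% with an assumed moderate one, and about 7% at most in the cases examined. The two effects pull in opposite directions. All sizes after Step 1 rest on assumed between-practice variation, covariate strength and, in the simulations, practice numbers.

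Nothing here threatens the validity of the trial. The reason to act is that a better-matched single analysis is available from data already held.

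**What to change.** Name one primary analysis that respects the stratified randomisation. Either of these would do:

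- a logistic model of attendance on arm, with practice and the baseline variables held for every randomised patient (age, sex, ethnicity, deprivation score, GP-recorded smoking status); or
- a Cochran-Mantel-Haenszel test stratified by practice.

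Label the crude chi-square supportive, and state in advance how very small practices will be pooled if needed. Reporting a risk difference with 95% CI beside the odds ratio would match the scale used for the sample size, but this is optional.

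The cost is a sentence or two in the analysis section. Practice is known from randomisation, the covariates are already extracted, and neither new data nor a change in sample size is required. If the full protocol or analysis plan already fixes this, it is enough to say so and cite it.
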